## Abstract

**Background:**

Despite decades of effort to reduce racial cancer disparities, Black people continue to die at higher rates from cancer than any other U.S. racial group. Because prevention is a key to the cost-effective and long-term control of cancer, the potential for cancer genetic counseling to play a central role in reducing racial cancer disparities is high. However, the benefits of genetic counseling are not equitable across race. Only 2% of genetic counselors self-identify as Black/African American, so most genetic counseling encounters with Black patients are racially discordant. Patients in racially discordant medical interactions tend to have poorer quality patient-provider communication and receive suboptimal clinical recommendations. One major factor that contributes to these healthcare disparities is racial bias. Drawing on findings from prior research, we hypothesize that genetic counselor providers’ implicit racial prejudice will be associated negatively with the quality of patient-provider communication, while providers’ explicit negative racial stereotypes will be associated negatively with the comprehensiveness of clinical discussions of cancer risk and genetic testing for Black (vs. White) patients.

**Methods:**

Using a convergent mixed methods research design, we will collect data from at least 15 genetic counseling providers, from two different institutions, and their 220 patients (approximately equal number of Black and White patients per provider) whose appointments are for a hereditary cancer condition. The data sources will include two provider surveys, two patient surveys, video- and/or audio-recordings of genetic counseling encounters, and medical chart reviews. The recorded cancer genetic counseling in-person and telehealth encounters will be analyzed both qualitatively and quantitatively to assess the quality of patient-provider communication and the comprehensiveness of clinical discussion. Those data will be linked to pre- and post-encounter survey data and data from medical chart reviews to test our hypotheses.

**Discussion:**

Findings from this multi-site study will highlight specific aspects of cancer genetic counseling encounters (patient-provider communication and clinical recommendations) that are directly associated with patient-centered outcomes (e.g., satisfaction, trust, genetic testing completion). Patient-provider communication and clinical recommendations are modifiable factors that can be integrated into current genetic counseling training curricula and thus can have immediate impact on genetic counseling training and practice.

## Background

Individuals with cancer are more likely to die from it if they are Black, [1] although hereditary cancer is distributed similarly across race [2, 3]. Because prevention is key to the cost-effective and long-term control of cancer, [4] the potential for cancer genetic counseling to play a central role in reducing racial cancer disparities is high. Genetic counselors address the medical, psychological, and familial concerns related to genetic disease, [5] including hereditary cancer. Yet, the benefits of genetic counseling are not equitable across race. Studies continue to show that Black patients with breast or colon cancer are less likely to discuss genetic evaluation or genetic counseling referral with their providers [6–8]. A systematic review also revealed racial disparities in genetic counseling experiences [9]. Despite a rapidly increasing discourse about, and recognition of, potential racial disparities in the genetic counseling process, only one study, to our knowledge, has directly compared Black and White patients [10]. In that study, Black women with breast cancer who had genetic counseling were less likely to have genetic testing. But, what happened during the genetic counseling session that may have led to this disparity was not examined.

Only 2% of genetic counselors in the US self-identify as Black/African American, while 90% self-identify as White American; [11] thus, genetic counseling encounters for Black patients will likely be racially discordant. This shockingly low number of Black genetic counselors (as a comparison, 5% of surgeons/physicians self-identify as Black/African American) [12] is a huge roadblock for the field of cancer genetic counseling to become an equalizer, because the quality of patient care tends to be poorer during racially discordant (vs. concordant) medical interactions in general [13–17]. One major factor contributing to such disparities is racial bias. Racial bias consists of prejudice (negative *feelings* toward racial minorities) and stereotyping (*beliefs* about racial minorities), both of which can operate at implicit and explicit levels [18, 19]. Bias at the implicit level reflects feelings and beliefs that are automatically and spontaneously activated; thus, it is relatively hard to control. In contrast, bias at the explicit level reflects a deliberate, effortful process and often takes into account social desirability concerns (e.g., desire to appear non-prejudiced). Both implicit and explicit bias reflect “true” feelings and beliefs; they simply reflect different psychological processes [19, 20]. In fact, consistent with prior research, [18–21] a recent study has shown that genetic counselors and genetic counseling trainees (we refer to them both as “genetic counseling providers” hereafter) displayed moderate pro-White/anti-Black implicit prejudice overall but no explicit prejudice [22]. Turning to implicit stereotyping, there was a trend for providers to associate White people with medical cooperativeness and Black people with medical non-cooperativeness. Finally, unlike physicians, genetic counseling providers, on average, reported explicitly that Black people are medically cooperative. However, they also reported that Black people are mistrustful of medical providers as well as of the healthcare system in general.

Distinguishing these forms of racial bias is important because they are associated with different aspects of healthcare. A recent review [23] provides evidence that providers’ greater implicit prejudice is associated with poorer quality patient-provider communication during racially discordant interactions, [24–28] which can further result in less patient satisfaction and trust in providers (Fig. 1) [29–31]. There is strong evidence that providers’ greater explicit negative stereotyping of Black patients is associated with suboptimal clinical recommendations for Black patients [21, 32, 33]. Drawing on findings from prior research, we developed a conceptual model highlighting genetic counselor bias, particularly implicit prejudice and explicit stereotyping, as major factors contributing to racial disparities in the genetic counseling process. We propose that patient-provider communication will be poorer for Black patients than for White patients (Path A) and that genetic counselors’ implicit prejudice toward Black people is negatively associated with the quality of patient-provider communication for Black patients, but not for White patients (Path C). We also propose that the content of clinical discussions will be lower in quality for Black patients than for White patients (Path B), and genetic counselors’ explicit negative stereotypes about Black people are negatively associated with the quality of clinical discussions for Black patients, but not for White patients (Path D). Finally, lower quality patient-provider communication and clinical discussions, in turn, will lead to Black patients’ negative perception of counselors and genetic counseling encounters (Paths E & F), ultimately contributing to racial disparities in patient-centered outcomes (Path G).

**Fig. 1 Fig1:**
[figure not shown]
Our conceptual model of the role of genetic counselor’s bias in racial disparities in the genetic counseling processes

Research in healthcare disparities, social psychology, communication science, and our research all point to the role counselor bias may play in racial disparities in genetic counseling processes. Indeed, early studies of *simulated* genetic counseling encounters show that pro-White/anti-Black implicit prejudice leads to less individualized communication with patients [35] and may influence how genetic counselors help patients process emotional and cognitive information [36]. However, there are at least two major knowledge gaps that discourage us from starting with intervention research to address counselor bias. First, there has been no empirical documentation of the nature of such disparities in the *naturalistic* clinical setting. It is plausible that genetic counselors may communicate with patients differently in the naturalistic clinical setting than in a simulated one. More critically, the perspective and voice of actual patients are missing. Prior research shows standardized patient ratings of providers’ communication are different from actual patients’ ratings [37]. Notable, too, is that most research has not investigated trainees/students, yet trainees provide a significant proportion of genetic counseling. In the U.S., one-third of cancer genetic counselors report working at a university medical center, and one-third claim “student supervision” as one of their roles [11]. Thus, any generalizable research must include genetic counseling performed by supervised trainees.

Second, genetic counseling research has been hampered by both a paucity of process research and uncertainty about what outcomes are important and how they should be measured [38, 39]. Recently, the National Society of Genetic Counselors Research Task Force noted a critical need to answer basic questions such as “What are, and how do we measure, the psychological, behavioral, medical, interpersonal, and economic outcomes of genetic counseling?” [40] We argue that racial disparities in the genetic counseling process matter because they may impact clinically meaningful patient outcomes. We recognize that the definition of “clinically meaningful patient outcomes” varies case to case. Our conceptual model focuses particularly on patient-centered outcomes, including genetic testing completion, trust in and bond with providers, empowerment, and perceived self-efficacy. These outcomes may be predictive of patients’ subsequent health-related behaviors (e.g., lifestyle changes, healthcare utilization) [41, 42] and are applicable to a wide range of medical contexts.

## Methods

The overarching goal of this research is to compare and contrast the nature of cancer genetic counseling encounters and patient-centered outcomes between Black and White patients in the naturalistic clinical setting. We will test our hypotheses by addressing four specific aims: **Aim 1**) To compare/contrast the nature of patient-provider communication by patient race (Black vs. White); **Aim 2**) To compare/contrast the clinical discussion content by patient race; **Aim 3**) To quantify the role of each type of counselor bias in patient-provider communication (Aim 1) and clinical discussion content (Aim 2); and **Aim 4)** To quantify the role of patient-provider communication and clinical discussion content with patient-centered outcomes (trust, satisfaction, therapeutic alliance, empowerment, genetic testing completion). These aims will be achieved through an observational study with a convergent mixed methods research design. Table 1 provides an overview of the study design.

**Table 1 Tab1:** An overview of the study designs

Aims	Data sources	Analyses	Goals
1	• Recorded encounters	Quantitative analyses of provider communication style and the overall quality of patient-provider communication Qualitative analyses of transcribed encounters for the four basic interaction structures	Identify specific aspects of patient-provider communication during cancer genetic counseling encounters that are different between Black and White patients
2	• Recorded encounters	Qualitative analyses of transcribed encounters for (1) the presence/absence of the key topics for risk communication and genetic test consent during cancer genetic counseling encounters that were identified by NCI; and (2) additional topics discussed during cancer genetic counseling encounters	Identify specific clinical discussion topics during cancer genetic counseling encounters that are different between Black and White patients
3	• Provider baseline survey • Patient baseline survey • Coded encounters	Quantitative analyses of associations between the four forms of provider bias and (1) patient-provider communication as well as (2) clinical discussion content that were identified in Aims 1 & 2	Identify specific aspects of patient-provider communication/clinical discussion topics that contribute to racial disparities in the cancer genetic counseling process and reflect provider bias
4	• Provider baseline survey • Patient baseline survey • Provider post-encounter survey • Patient post-encounter survey • Coded encounters	Quantitative analyses of associations between (1) patient-provider communication as well as (2) clinical discussion content that were identified in Aims 1 & 2	Identify specific aspects of patient-provider communication/clinical discussion topics that contribute to racial disparities in the cancer genetic counseling process and in patient-centered outcomes

Our conceptual model of racial disparities in the cancer genetic counseling process is applicable to many genetic counseling encounters. However, this research will focus on pre-test cancer genetic counseling encounters for both theoretical and methodological reasons. Traditional cancer genetic counseling involves at least two encounters with patients having genetic testing: [1] a pre-test session involving risk assessment and informed consent; and [2] a post-test session in which risks and medical management are re-assessed in light of genetic test results. More cancer genetic testing is being facilitated by non-genetics providers (e.g., direct-to-consumer testing, mainstream testing by oncology providers). In such cases, genetic counselors may shift to involvement only after testing is completed, and often only if patients test positive. However, we chose to focus on pre-test genetic counseling sessions for a number of reasons. First, the counseling elements in pre-test sessions are more uniform than in post-test sessions, especially in light of multigene panel testing consent, which, by necessity involves discussions that are often not specifically focused on individual genes and related medical management implications [43]. Focusing on pre-test cancer genetic counseling encounters also minimizes inherent variability across pre- vs. post-genetic testing contexts as well as across different areas/specialties of genetic counseling, providing greater ability to test our conceptual model. Second, for about nine out of 10 referred patients, genetic test results will be negative; [2] in most of these cases, the risk assessment and medical management recommendations content will remain largely unchanged. Finally, studies show that genetic testing completion is lower when pre-test counseling is provided by genetics providers, [44] compared with non-genetics providers. By focusing on pre-test genetic counseling, we can gain insight into predictors of genetic testing completion, especially whether racial bias plays a role. After validating our conceptual model in the context of pre-test cancer genetic counseling, our future work can examine whether this model is generalizable to other genetic counseling contexts. Such empirical evaluation of the generalizability of the conceptual model will further contribute to theory development.

### Participants

We will recruit *at least* 15 genetic counseling providers (both genetic counselors and MS genetic counseling trainees) and 220 patients (approximately equal number of Black and White patients for each provider) from two different institutions that serve diverse patient populations. The eligibility criteria for *genetic counseling providers* are that they are either American Board of Genetic Counseling certified genetic counselors or trainees in at least the second rotation for cancer genetic counseling. Even if there are too few male or minority providers to conduct meaningful inferential statistics, we will not exclude anyone based on sex/gender or race/ethnicity. Inclusion of all providers may be hypothesis generating for future work. The eligibility criteria for *patients* are: 1) self-identify as either Black/African American or White American; 2) ≥ 18 years old; 3) have an upcoming cancer genetic counseling appointment primarily focused on assessment of, and/or counseling for, a hereditary cancer condition with one of the participating providers at any of the recruitment sites; and 4) be able to comprehend all documents in English, written at a 6th grade reading level.

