#### Professional information

We will assess status (genetic counselor vs. genetic counseling trainee), years in practice (genetic counselor only), years at the current institution (genetic counselor only), or year in training (genetic counseling trainees only).

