Aim 1 (to compare/contrast the nature of patient-provider communication by patient race) examines Path A in our conceptual model. To test Path A, first, we will examine a numerical and graphical summary of descriptive statistics that will inform the distribution of the 15 outcomes (14 categorical variables and the overall patient-provider communication) and that may require data transformation. Then, we will conduct two separate analyses for communication and linguistic patterns. To examine how genetic counseling providers’ communication style differs by patient race, we will identify covariates by conducting bivariate correlations among all 15 outcomes and factors that were assessed in the baseline surveys (e.g., provider/patient demographics including sex, provider professional characteristics, patient perceived discrimination). Next, we will estimate a linear regression model for each outcome with the main effect of patient race, the main effect of care modality, a two-way interaction between patient race and care modality, and covariates identified as highly correlated with the outcomes. We will use GEE (which controls for the dependence in outcomes due to patients nested within providers) in these regressions, instead of multilevel modeling (which models the nonindependence in data), because there will not be enough upper-level units (i.e., counselors) to model random effects in our data. We will use the Bonferroni correction [93, 94] to address family-wise errors due to multiple comparisons. To examine which specific linguistic patterns differ by patient, we will conduct analyses in similar steps described above. First, we will identify highly correlated covariates by computing bivariate correlations among all quantified linguistic patterns and factors assessed in the baseline surveys. Next, we will conduct a regression for each quantified linguistic pattern with the main effect of patient race, the main effect of care modality, a two-way interaction between the two, and covariates using GEE and the Bonferroni correction. Type of regressions will depend on the measurement units.

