Aim 2 (to compare/contrast the clinical discussion content by patient race) examines Path B in our conceptual model. We will examine which topics significantly differ between Black and White patients. First, we will identify covariates that may impact clinical discussion content by computing bivariate correlations among all topics and factors assessed in the baseline surveys. All significant factors will be included in the main analyses as covariates. In the main analyses, we will conduct a logistic regression (the dichotomous outcome) and a linear regression (the continuous outcome) for each topic with the main effect of patient race, the main effect of care modality, a two-way interaction between the two and covariates using GEE and the Bonferroni correction.

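### No listed model contains a site term, so differences between the two institutions can confound the Aim 3 provider-bias main effects and the Aim 4 associations

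*Protocol article*

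**What the plan says.** The Participants section plans at least 15 "genetic counseling providers (both genetic counselors and MS genetic counseling trainees) and 220 patients", recruited "from two different institutions that serve diverse patient populations", with an "approximately equal number of Black and White patients for each provider". The split of providers between the institutions is not given.

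The Statistical analysis section sets out the models:

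- **Aim 1:** "the main effect of patient race, the main effect of care modality, a two-way interaction between patient race and care modality, and covariates". The covariates come from a screen: "we will identify covariates by conducting bivariate correlations among all 15 outcomes and factors that were assessed in the baseline surveys".
- **Aim 2:** the same structure for each topic, with covariates found by "computing bivariate correlations among all topics and factors assessed in the baseline surveys".
- **Aim 3:** patient race, two bias measures, care modality, all their interactions, and covariates screened from the baseline surveys.
- **Aim 4:** the communication and discussion aspects kept from the partial-correlation step, care modality, and covariates screened from the two baseline surveys and the provider post-encounter survey.

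GEE is used to handle patients nested within providers. Table 2 and the Measures section describe the survey content. The nearest item to site is "years at the current institution (genetic counselor only"; this is tenure, not which institution, and trainees are not asked it.

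**The concern.** Site is a design feature of a two-institution study, and it may be related both to who the providers are and to how sessions run. Bias is measured once per provider, so a bias main effect rests on about 15 distinct values spread over two institutions. Suppose one institution has higher bias scores and also shorter sessions, fewer topics or a different communication style for all patients. A model without site will then credit that difference to bias.

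Aim 4 has the same structure. Test completion is read from medical records up to 6 months after the session. An institution whose routine makes testing easier, and whose counselors also communicate differently, would show an association between communication and completion that reflects the institution.

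The results are meant to be acted on. Communication styles that stay significant in Aim 3 are to be called key contributors to disparities that reflect bias, and aspects that stay significant in Aim 4 are to be treated as possible intervention points.

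**Working it through.** The plan gives no figure on this point, so there is none to reproduce. The check has three parts.

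**1. Text check.** Each model's terms (Statistical analysis, Aims 1 to 4) were compared with the survey content (Table 2 and Measures). No model contains site, and no listed survey item records institution. Care modality, by contrast, is forced into every model. GEE clustering on provider corrects standard errors for dependence; it does not remove a difference in means between institutions.

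**2. Induced correlation.** Assumptions: two sites of equal size, within-site variance 1 for both bias and outcome, the same gap δ (in SDs) between sites on both, and no true effect. Then:

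- between-site covariance = δ²/4
- total variance of each variable = 1 + δ²/4
- r = (δ²/4) / (1 + δ²/4)

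| δ | δ²/4 | r |
|---|---|---|
| 0.5 | 0.0625 | 0.0625/1.0625 = 0.06 |
| 0.63 | 0.0992 | 0.0992/1.0992 = 0.09 |
| 0.8 | 0.16 | 0.16/1.16 = 0.14 |

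With a share p of the sample at one site, δ²/4 becomes p(1 − p)δ². This is largest at p = 1/2, so an uneven split induces less. The formula applies equally to a communication score and a continuous outcome in Aim 4. It does not give a figure for test completion, which is binary.

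For scale, the plan's target d = 0.2 converts to r = 0.2/√(0.2² + 4) = 0.2/√4.04 = 0.0995, using the formula for two equal groups.

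**3. Simulation, and which Aim 3 terms are exposed.** Assumptions: 15 providers (8 and 7 per site), 15 patients each (N = 225), race about 1:1 within provider, within-provider ICC 0.05, true bias effect zero, and 1,000 runs per scenario. The model was linear, with race, one bias score and their product, and provider-clustered standard errors. It is simpler than the plan's Aim 3 models. The adjusted version added site and site-by-race together. Slopes are in outcome SD per SD of bias.

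Bias slope averaged over race, with a plain site shift of 0.5 SD in the outcome:

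| Site gap in bias | Slope, site omitted | Rejection at nominal 5% | Slope, adjusted | Rejection, adjusted |
|---|---|---|---|---|
| 0 | 0.00 | 10.4% | 0.00 | 10.4% |
| 0.5 SD | 0.06 | 14.5% | 0.00 | 11.0% |
| 1.0 SD | 0.11 | 27.2% | 0.00 | 12.6% |

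With no site difference of any kind, rejection was already 9.4% (site omitted) and 9.7% (adjusted). The excess over 5% that remains after adjustment therefore comes from having few clusters, not from site.

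Race-by-bias interaction:

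| Site difference in outcome | Site gap in bias | Site omitted | Adjusted |
|---|---|---|---|
| Plain shift, 0.5 SD | 0.5 SD; 1.0 SD | 0.01; 0.00 | 0.00; 0.00 |
| Race difference differs by 0.5 SD | 0.5 SD; 1.0 SD | 0.07; 0.10 | 0.01; 0.00 |

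The interaction is unaffected by a plain site shift, because each provider sees both races in about equal numbers and the shift cancels in the within-provider race difference. The cancellation fails when the race difference itself varies by site.

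**The case against.** **Open candidate lists.** The examples of screened factors are introduced as examples, and this is an article that condenses a longer protocol. A reader might infer that site cannot enter any model by any route. The documents do not support that: an unlisted institution item could exist, or a fuller plan could add site. What stands is narrower. The examples are examples of survey factors, no listed survey item is institution, and even an unlisted item would enter only if it passed the correlation screen.

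**The hypothesis-testing terms.** A reader might infer that the tests of Paths C and D are confounded by any site difference. They are not. The Background states those paths as associations for Black but not White patients, which is the race-by-bias interaction, and race balance within provider largely protects it from a plain site shift. This objection stands, and it limits the point to the bias main effects, the Aim 4 associations, and the interactions only when the race difference varies by site.

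**Providers and sites.** It is tempting to treat site as strictly a provider-level variable. The article does not say that each provider works at one institution only, and trainees rotate. If some providers work at both, site varies partly within provider; the omission remains.

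**Partial proxies.** Care modality is in every model. Trainee status, frequency of seeing Black patients, and trust and satisfaction tied to the specific health system can be screened in. They may track site, but they are not site.

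**Adjustment is not free.** Each Aim 3 model already has three terms that vary only between providers (two bias measures and their product), plus any provider covariates. If bias truly differs between institutions, adjusting for site also removes that part of its variation. This is a fair trade-off to state.

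**Conclusion.** The point holds in limited form. Followed as written, the plan leaves the two institutions unadjusted. The bias main effects in Aim 3 and the communication and discussion associations in Aim 4 are open to confounding by site. The Aim 1 and 2 race contrasts and the Aim 3 race-by-bias terms are largely protected from a plain site shift. The Aim 3 interactions are exposed if the race difference differs between sites.

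The size depends wholly on assumed gaps, because the article gives no site-level figures. Equal gaps of 0.5 to 0.8 SD in bias and outcome induce a correlation of about 0.06 to 0.14. If bias does not differ between sites, the bias slope is not distorted. A reader might infer that a site difference could account for the whole target effect, since d = 0.2 converts to r of about 0.10. The documents do not support that as a finding: the gaps are hypothetical, and the article does not say how its d is defined for a continuous predictor.

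This is an inexpensive safeguard worth adding, not evidence that the planned results will be wrong.

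**What to change.** 1. State that site enters every Aim 3 and Aim 4 model as a fixed two-level factor, whatever the correlation screen shows. It is optional in Aims 1 and 2.
2. For the Aim 3 race-by-bias terms, report a sensitivity analysis that adds site-by-race. A site main effect alone does not address a race difference that varies by site.
3. Report the number of providers per site, and whether any provider works at both.

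**Cost.** Institution is known from recruitment, so no new data are needed. Each site term uses about one provider-level degree of freedom out of about 15. If the split of providers is very uneven, the site term will be imprecise and will mostly represent a few individuals; the results should then be shown with and without it.
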